**PROPOSED STARTING DATE: November 1, 2006 DURATION: 24 Months**

**Abbreviations:**

AQ Adverse Event (s)

AS Acquired Immunodeficiency Syndrome

CRF(s) Case Record Form (s)

DSMB Data Safety Monitoring Board

EDT Early diagnosis and treatment of malaria

HIV Human Immunodeficiency Virus

IPT Intermittent Preventive Treatment

IPTp Intermittent Preventive Treatment in pregnancy

ITNs Insecticide treated mosquito net(s) or material (s)

LLIN Long lasting insecticide treated nets

LSHTM London School of Hygiene and Tropical Medicine

MCH Maternal and Child Health

OPD Outpatients Department

PCR Polymerase Chain Reaction

PI Principal Investigator

pLDH Plasmodium Lactate Dehydrogenase

SAE(s) Serious Adverse Event(s)

SP Sulphadoxine Pyrimethamine

TBA Traditional Birth Attendant

WBC White blood cell

WHO The World Health Organisation

**RESEARCH PROPOSAL**

# TITLE

The effectiveness, cost and cost effectiveness of intermittent preventive treatment or screening and treatment of malaria in pregnancy among women using long lasting insecticide treated bed net: a randomised controlled trial.

# BACKGROUND & RATIONALE

*Plasmodium falciparum* infection in pregnancy is associated with an increased risk of maternal and foetal complications including maternal anaemia and low birth weight (Brabin 1991; Menendez 1995). The pattern and severity of complications depend on gravidity, gestational age, age and HIV/AIDS and a woman’s pre-existing immunity, which is influenced by the local malaria transmission profile (WHO 2004). The WHO has recommended a package of interventions for preventing and controlling malaria infection in pregnancy in endemic areas which includes; the early diagnosis and treatment of malaria (EDT), intermittent preventive treatment during pregnancy (IPTp) using Sulphadoxine-Pyrimethamine (SP) and the use of insecticide treated bed nets (ITNs) (WHO 2004).

The policy of SP-IPTp for pregnant women has been shown to be efficacious, easy to administer, safe and tolerable (Pari*se et a*l. 1998; Verhoe*ff et a*l. 1998; Shulm*an et a*l. 1999; Rogers*on et a*l. 2000; van Ei*jk et a*l. 2004; Kayent*ao et a*l. 2005). Currently, SP-IPTp has been rated as having the most favourable effectiveness profile in terms of its low cost, compliance and reduced morbidity and mortality resulting from the prevention of maternal anaemia and low birth weight (Goodm*an et a*l. 2001; Newm*an et a*l. 2003). However, implementation of IPTp in most settings is limited by social, cultural, economic and operational challenges despite good coverage of antenatal services (Rogers*on et a*l. 2000; Hol*tz et a*l. 2004). In Ghana, implementation of SP-IPTp is currently being piloted in only 20 of its 110 districts (Dod*oo et a*l. 2005). The resistance to SP has been spreading across sub-Saharan Africa and thus the effectiveness of SP-IPTp has been questioned (Newm*an et a*l. 2003). There are very limited antimalarial drugs with plasma half life comparable to SP (e. g. Mefloquine) that could be used to replace SP for IPTp in areas with high SP resistance. Furthermore there is very limited data on the efficacy and safety during pregnancy of drugs with potentials to replace SP for IPTp. Thus evaluation of safety and efficacy of antimalarials drugs suitable for IPTp and alternative approaches to reduce the burden of malaria during pregnancy are needed urgently.

A recent study of rapid diagnostic test (RDT) screening and treatment of parasitaemic pregnant women with amodiaquine (AQ) or SP singly or their combination in Ghana showed that this approach can reduce the prevalence of low birth weight by 30% and the prevalence of severe maternal anaemia (Hb < 8.0g/dl) at delivery by 45% (Tagb*or et a*l. 2006). These protective effects are similar to those obtained with SP-IPTp in Mali (Kayent*ao et a*l. 2005); Kenya (Pari*se et a*l. 1998; Shulm*an et a*l. 1999; Nja*gi et a*l. 2003) and Malawi (Verhoe*ff et a*l. 1997; Rogers*on et a*l. 2000). Although RDTs are not quantitative (Wongsrichanalai 2001) and peripheral parasite density in pregnancy may not correlate with placental parasitaemia, the use of OptiMAL® dipsticks to detect circulating parasite-specific lactate dehydrogenase (pLDH) may be of public health significance. The antenatal RDT screening was feasible and the cost was comparable to that of microscopy which costs an average of 10,000 and 15,000 cedis (1 US$=9100 cedis) in public and mission hospitals respectively.

The results of initial studies of the effects of ITNs on maternal anaemia and low birth weight were inconsistent because of the complexity of factors that determine acquisition and continued use of the nets. For example studies in Ghana (Brow*ne et a*l. 2001) and Kenya (Shulm*an et a*l. 1998) did not find any effect on malaria and anaemia in pregnancy following the use of insecticide impregnated bed nets; whilst other studies in the mesoendemic area of the Thai-Burmese border (Dol*an et a*l. 1993) and in The Gambia (D'Alessand*ro et a*l. 1996) found reductions in maternal anaemia and low birth weight with the use of ITNs.

However, a recent study of the impact of large scale use of ITNs among Kenyan pregnant women (ter Kui*le et a*l. 2003; ter Kui*le et a*l. 2003) showed significant reductions in malaria related adverse pregnancy outcomes. It is not clear though, how much extra benefit there is in combining use of ITNs and IPT during pregnancy (Nja*gi et a*l. 2003; Mba*ye et a*l. 2006).

There is currently great international support and momentum to increase the coverage of ITNs use among pregnant women. Thus while looking for alternative drugs for IPT in areas with SP resistance we have to consider the additional benefits of the combination of ITN and IPT over ITN with effective case management approach and the potential drug related adverse outcomes of drugs used for IPTp. The RDT screening and treatment with an effective antimalarial of those with a positive RDT test will reduce the number of women that would be exposed to drugs. Although some women with placental malaria may be missed by the RDT screening, it can be argued that the proportion of women with placental malaria missed by RDT would be minimal if all women used an ITN and that the risk of missed placental malaria will be offset by the reduction in women exposed to antimalarials of uncertain safety profile unnecessarily.

We are proposing this follow up study to determine whether active case finding and management is as effective as intermittent preventative treatment for the control of malaria during pregnancy. A two-armed non-inferiority randomised trial using SP in both arms (LLIN+ IPTp or LLIN + RDT & treatment) is appropriate to address this question. However, if SP is not very effective, a difference may not be found between the two arms since the effect of SP as IPT or treatment would be minimal and the effect of LLIN would be similar in both arms. We cannot replace SP with another effective antimalarial in the IPTp arm since the safety profile of potential antimalarial drugs that could replace SP are not adequately established to be useful for IPTp. A two arm study of LLIN + SP-IPTp and LLIN + RDT & AQ+AS treatment will not be appropriate to prove the principle that LLIN + RDT & treatment is not inferior to LLIN + IPTp since AQ+AS is likely to be more efficacious than SP and this would bias our observation. Thus we propose a three arm trial: (1) LLIN plus SP-IPTp; (2) LLIN plus RDT and treatment with SP (3) LLIN plus RDT and treatment with AQ+AS.

AS+AQ is the first line drug of choice for treatment of uncomplicated malaria in Ghana. However there is very little safety data on the use of AS+AQ for the treatment of malaria during pregnancy and the safety data collected in this study will be very useful for informing the national drug policy for treatment of malaria during pregnancy.

# **METHODS**

## General objective

To show that the LLIN plus RDT screening and treatment strategy is not inferior to LLIN plus SP-IPTp in reducing the burden of malaria during pregnancy.

## Specific objectives

Primary

1. To demonstrate that the prevalence of severe anaemia (Hb < 8g/dl) at 34 to 36 weeks of gestation in the LLIN plus RDT screening and case management arm is not greater than that in the LLIN plus IPTp arm.

Secondary

1. To demonstrate that the prevalence of low birth weight (BW < 2500g) at delivery or within 72 hours after delivery in the LLIN plus RDT screening and case management arm is not greater than that in the LLIN plus IPTp arm.
2. To demonstrate that the prevalence of anaemia (Hb < 11g/dl) at 34 to 36 weeks of gestation in the LLIN plus RDT screening and case management arm is not greater than that in the LLIN plus IPTp arm.
3. To demonstrate that the prevalence of placenta parasitaemia at in the LLIN plus RDT screening and case management arm is not greater than that in the LLIN plus IPTp arm.
4. To demonstrate that the incidence of spontaneous abortions, intrauterine deaths/stillbirths, neonatal and maternal mortality and developmental delays in the LLIN plus RDT screening and case management arm is not greater than that in the LLIN plus IPTp arm.
5. To demonstrate that the cost per case of (1) severe maternal anaemia averted (2) maternal anaemia averted (3) peripheral malaria averted and (4) placenta malaria averted is not higher in the LLIN plus RDT screening and case management arm than in LLIN plus SP-IPTp arm.

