## Study outcomes

Primary

- 1. Prevalence of severe maternal anaemia (Hb < 8g/dl) at 34 to 36 weeks of gestation.

Secondary

1. Prevalence of low birth weight (BW < 2500g) at delivery or within 72 hours of delivery.
2. Prevalence of maternal anaemia (Hb < 11g/dl) at 34 to 36 weeks of gestation.
3. Prevalence of placenta parasitaemia.
4. Incidence of post intervention malaria cases
5. Proportions of congenital anomalies in live births among the intervention groups stratified by gestation, gravidity, parity and age.
6. Proportions of spontaneous abortions, intrauterine death, stillbirths, neonatal and maternal mortality and pre-term deliveries.
7. Cost per severe maternal anaemia averted.
8. Cost per (non-severe) maternal anaemia averted.
9. Cost per peripheral malaria case averted.
10. Cost per placenta malaria averted.

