## ***Sample size***

The prevalences of severe anaemia at delivery and low birth weight have been shown to be about 12% and 5.7% respectively among Gambian multigravidae who received varying doses of SP-IPT (Mba*ye et a*l. 2006). In the absence of local data from the proposed study site, we estimate that the prevalences of severe anaemia in the third trimester and low birth weight will be 12% and 6% respectively in the LLIN +SP-IPTp arm of this study, similar to the Gambian population.

For trial planning we have set a non-inferiority margin of 5%. This means we would deem the LLIN + RDT screening with SP or AQ+AS treatment options to be inferior to the LLIN +SP-IPTp option if the prevalence of severe anaemia at 34 to 36 weeks is 5% greater in the LLIN+RDT with SP or AS+AQ treatment arm than that is observed in the LLIN+SP-IPT arm. Since we expect the prevalence of severe anaemia in the LLIN +SP-IPTp arm would be 12%, we need 887 women per arm to detect a 5% difference between the two study arms at 95% significance with 90% power. Considering a 20% dropout rate we need 1110 women per arm.

Setting a non-inferiority margin of 5% seems clinically and statistically relevant; and yields a sample size that makes the execution of the study feasible within the time frame and with the resources available. Choosing a smaller margin than 5%may be too tight requiring large sample size of over 2000 per arm which might not be feasible and achievable within the time frame; a larger margin than 5% may be too liberal to compare the public health impact of these interventions.

We estimate that 925 women per arm can show with 90% power at 95% significance level and accounting for a 20% dropout rate, that the prevalence of low birth weight associated with the LLIN + RDT screening with or without SP or AQ+AS treatment is no worse than LLIN + SP-IPTp by a margin of 4%.

Since, a sample size of 1110 per arm is adequate to detect any effects of the interventions on both birth weight and maternal Hb, a total of 3330 pregnant women will be recruited into this study.

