## Delivery and Postpartum Follow-up

1. The midwives will record all birth weights and note any stillbirths and perinatal deaths.
2. Midwives will record all congenital deformities for verification and confirmation by a clinician.
3. Visit all women and babies at 6 to 8 weeks post delivery to obtain reports of any neonatal adverse events such as deaths or morbidity.
4. At 6 weeks post partum, if a woman has peripheral parasitaemia she will be treated with SP and followed up for parasite clearance on days 14 and 28 post treatment. If there is no parasite clearance on day 14 and/or day 28 a course of rescue medication (quinine) will be given. This part of the study is necessary to assess the efficacy of SP to clear parasitaemia.

Figure 1: - Flow chart of proposed study design

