**RDT screening and SP case management arm**

Record pregnancy and delivery outcomes (abortions, SB, abnormalities); BW and neonatal jaundice.

Follow-up child at 6 to 8 weeks

Check blood slide of the mother for MP. If positive give a course of SP and follow up on day 14 and day 28

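### Secondary objective 4 promises a demonstration on developmental delay, which no listed outcome or visit assesses, and on maternal death, for which 1110 women per arm are too few

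*Protocol*

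**What the plan says.** The protocol's Specific objectives section lists, as secondary objective 4, a demonstration covering pregnancy loss, deaths and child development: "neonatal and maternal mortality and developmental delays in the LLIN plus RDT screening and case management arm is not greater" than in the IPTp arm.

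The matching item under Study outcomes is secondary outcome 6: "Proportions of spontaneous abortions, intrauterine death, stillbirths, neonatal and maternal mortality and pre-term deliveries". It leaves out developmental delay and adds pre-term delivery, which the objective does not mention.

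Under Delivery and Postpartum Follow-up, data at birth come from the midwives: "The midwives will record all birth weights and note any stillbirths and perinatal deaths". They also record congenital deformities. The only later child contact is described as "Visit all women and babies at 6 to 8 weeks post delivery to obtain reports of any neonatal adverse events", with deaths or morbidity given as examples. The flow chart (Figure 1) says only "Follow-up child at 6 to 8 weeks", and says so for each of the three arms.

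The Sample size section gives margins for two outcomes only: 5 percentage points for severe anaemia and 4 for low birth weight. It describes 1110 women per arm as adequate for birth weight and maternal haemoglobin. No expected rate is given for any event in objective 4.

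**The concern.** Two parts of the objective cannot be delivered by the design as written.

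First, an objective needs a measured outcome. Developmental delay is named once, in the objective, and nowhere else. A statistical analysis plan can define an analysis, but it cannot create data that no visit collects.

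Second, demonstrating that a risk is not greater requires enough events to rule out a meaningful increase. Maternal death is likely to be the rarest event in the list. If only a handful of deaths occur, the interval will be compatible with both benefit and serious harm. The protocol's background section says that safety data on AS+AQ in pregnancy will inform national drug policy, so a claim of this kind on maternal death should not be promised if the trial cannot support it.

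**Working it through.** **Developmental delay, text against text**

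- Objective 4: developmental delay is to be shown not greater with screening.
- Study outcomes: none of the ten secondary outcomes is developmental.
- Delivery records: birth weight, stillbirths, perinatal deaths, congenital deformities.
- Visit at 6 to 8 weeks: reports of neonatal events.
- Flow chart: a child follow-up at the same age, with no content stated.

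No definition, instrument or age of assessment appears anywhere.

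**The protocol's own sample size, reproduced first**

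Inputs from the Sample size section: "we expect the prevalence of severe anaemia in the LLIN +SP-IPTp arm would be 12" percent; "For trial planning we have set a non-inferiority margin of 5" percentage points; "we need 887 women per arm to detect a 5% difference between the two study arms at 95% significance with 90% power".

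n = 2p(1−p)(1.96 + 1.2816)² / margin² = 2 × 0.12 × 0.88 × 10.507 / 0.05² = 887.7, and 888 / 0.8 = 1110.

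For low birth weight, 2 × 0.06 × 0.94 × 10.507 / 0.04² = 740.8, and 740 / 0.8 = 925. Both stated figures reproduce and are not in question.

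**Maternal death**

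Assumptions: the death rate p is not in the protocol, so a range of 0.1% to 1% is used. True risk is equal in both arms, there are 1110 women per arm, and nobody is lost. The benchmark is exclusion of a doubling.

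- Expected deaths per arm: e = 1110 × p.
- Upper 95% limit of the risk ratio when the observed ratio is 1: exp(1.96 × √(1/e + 1/e)).
- Exact power: given T deaths in total, the number in the screening arm is binomial with probability 2/3 if the true ratio is 2. A doubling is excluded when the lower tail is at most 0.025. This is averaged over Poisson counts with mean e in each arm.

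Worked example at 0.3%: e = 3.33; √(2/3.33) = 0.775; exp(1.96 × 0.775) = 4.57.

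| Assumed rate | Deaths per arm | Upper limit of ratio | Exact power, 1110 v 1110 | Both screening arms pooled, 2220 v 1110 | 888 v 888 (after 20% dropout) |
|---|---|---|---|---|---|
| 0.1% | 1.1 | 13.9 | 1% | 3% | 1% |
| 0.3% | 3.3 | 4.6 | 9% | 11% | 6% |
| 1% | 11.1 | 2.3 | 30% | 37% | 24% |

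As a plain check on the exact method, suppose no deaths occur in the screening arm. Three deaths in the IPTp arm give (1/3)³ = 0.037, which is not enough. Four give (1/3)⁴ = 0.012. So even the most favourable split needs at least four deaths, all in the IPTp arm.

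Events needed per arm to exclude a doubling with 90% power: 2 × (1.96 + 1.2816)² / (ln 2)² = 21.01 / 0.4805 = 43.7. In women per arm that is 43,740 at 0.1%, 14,580 at 0.3% and 4,374 at 1%.

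**Where the problem stops**

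With 1110 per arm, exact power to exclude a doubling is 57% at an assumed rate of 2%, 76% at 3% (81% by the log risk ratio) and about 94% at 5%.

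**The case against.** Several points on the other side have force.

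- *The wording is a template.* Secondary objectives 2 and 3 (anaemia and placental parasitaemia) use the same formula without a sample size of their own, and the Sample size section claims adequacy only for birth weight and haemoglobin. This is true, and it makes an oversight likely. It does not make the objective achievable for maternal death.
- *A missing margin may sit in the statistical analysis plan.* This stands. A reader might infer that the lack of a margin for objective 4 is itself the fault. It is not, since the plan is not shown. The number of deaths, however, is fixed by the design.
- *A doubling is not the protocol's criterion.* Correct: the stated margins are absolute. But carrying the 4-point margin over to an event at 1% would tolerate 5%, a fivefold rate, so it would offer no useful protection.
- *A difference-based interval looks better.* At 1% the half-width is 1.96 × √(2 × 0.01 × 0.99 / 1110) = 0.83 points, and (1 + 0.83)/1 = 1.83 seems to exclude a doubling. That conversion treats the control rate as known and is not a limit for the risk ratio. The ratio limit is 2.3.
- *The 6 to 8 week visit is open-ended.* It collects morbidity, so a reader might go too far in inferring that no infant health data will exist. The supported statement is that no developmental assessment is named.

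A reader might also infer that the whole of objective 4 is underpowered. The documents do not support that. They give no rate for abortion, stillbirth or neonatal death, and if any of these runs near 5% the sample is adequate for excluding a doubling. Nor does the protocol say that a non-significant difference would count as success; for severe anaemia it judges against a margin.

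**Conclusion.** The point holds in two limited parts. The developmental part of objective 4 cannot be met, because nothing in the outcome list or the follow-up assesses development; this rests on the text alone. The maternal-death part rests on an assumed rate and on doubling as the benchmark. The conclusion is the same at each tabulated rate from 0.1% to 1%: about 1 to 11 deaths per arm, upper limits from 13.9 down to 2.3, and power of 1% to 30%, or at most 37% with both screening arms pooled. The same reasoning applies to any other event at or below about 1 to 2%. It does not reach commoner events, so barring every non-inferiority conclusion under objective 4 would go too far. The primary objective and the sample size are unaffected.

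**What to change.** Delete developmental delay from secondary objective 4, and reconcile the objective with secondary outcome 6, which lists pre-term delivery. Keeping developmental delay would instead need a defined assessment at a stated age, added to the outcomes and the follow-up, which is a larger change.

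For maternal mortality, and for any other event expected at or below about 1 to 2%, reword along these lines: *to estimate and compare between arms, with 95% confidence intervals, the proportion of women with the event; no non-inferiority conclusion is drawn.* A non-inferiority aim for commoner losses may stay, provided a margin is stated.

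The cost is the rewording of one objective and a less ambitious stated claim. No visit, sample size or primary analysis changes.

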## Study outcomes

Primary

- 1. Prevalence of severe maternal anaemia (Hb < 8g/dl) at 34 to 36 weeks of gestation.

Secondary

1. Prevalence of low birth weight (BW < 2500g) at delivery or within 72 hours of delivery.
2. Prevalence of maternal anaemia (Hb < 11g/dl) at 34 to 36 weeks of gestation.
3. Prevalence of placenta parasitaemia.
4. Incidence of post intervention malaria cases
5. Proportions of congenital anomalies in live births among the intervention groups stratified by gestation, gravidity, parity and age.
6. Proportions of spontaneous abortions, intrauterine death, stillbirths, neonatal and maternal mortality and pre-term deliveries.
7. Cost per severe maternal anaemia averted.
8. Cost per (non-severe) maternal anaemia averted.
9. Cost per peripheral malaria case averted.
10. Cost per placenta malaria averted.

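### Secondary outcome 5 counts congenital anomalies in live births only, so an anomaly in a stillborn infant falls outside the trial's only anomaly outcome

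*Protocol*

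**What the plan says.** Under Study outcomes, the fifth secondary outcome is "Proportions of congenital anomalies in live births among the intervention groups stratified by gestation, gravidity, parity and age". The sixth is "Proportions of spontaneous abortions, intrauterine death, stillbirths, neonatal and maternal mortality and pre-term deliveries". No other outcome mentions anomalies, and outcome 6 does not classify deaths by whether an anomaly was present.

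Delivery and Postpartum Follow-up has two separate instructions: "The midwives will record all birth weights and note any stillbirths and perinatal deaths" and "Midwives will record all congenital deformities for verification and confirmation by a clinician". Neither limits the recording of deformities to infants born alive. The flow chart (Figure 1) gives one combined instruction in each arm: "Record pregnancy and delivery outcomes (abortions, SB, abnormalities); BW and neonatal jaundice".

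The Background says, of AS+AQ in pregnancy, that "the safety data collected in this study will be very useful for informing the national drug policy for treatment of malaria during pregnancy".

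**The concern.** Outcome 5 uses less than the delivery procedures ask staff to collect, and no reason is given. There are two consequences.

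- **Undercount.** Anomalies in stillborn infants drop out of the only measure of anomalies. The event is likely to be rare, so a few omitted cases per arm are a noticeable part of the total.
- **Selection after randomisation.** Whether a fetus is born alive is settled after allocation. The protocol itself treats stillbirth as something the strategies might change, since it is part of secondary objective 4 and of outcome 6. Live births are therefore a subgroup formed after randomisation. If affected fetuses die more often in one arm, that arm's live-birth anomaly proportion falls and it looks better on this outcome.

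The safety data on AS+AQ are meant to inform national policy, so a defined anomaly outcome should not depend on fetal survival where this is easily avoided.

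**Working it through.** **1. Where does an anomalous stillbirth go?**

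| Place in the protocol | Live-born with anomaly | Stillborn with anomaly |
|---|---|---|
| Delivery procedures | Recorded, confirmed by a clinician | Stillbirth noted; the anomaly is covered if the instruction on deformities is read as including stillborn infants |
| Outcome 5 | Numerator and denominator | Neither |
| Outcome 6 | Only if the infant dies or is pre-term | Counted as a death, without the anomaly |

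The gap follows from the text alone.

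**2. The plan's own figure.** The protocol states no anomaly or stillbirth rate, so there is none to reproduce. The only planned number used below is 1110 women per arm. It checks: 2 × 0.12 × 0.88 × (1.960 + 1.282)² / 0.05² gives 888 (887 stated), and 888 / 0.8 = 1110.

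**3. Illustrative size.** All rates are assumptions: stillbirths s = 2 to 4% of births, anomalies in live births a = 1 to 2%, anomalies in stillbirths b = 5 to 15%. N = 1110 births per arm assumes one birth per woman and no losses.

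- Anomalies in live births = N(1 − s)a
- Anomalies in stillbirths = N·s·b
- Share left out = s·b / [s·b + (1 − s)a], in which N cancels

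| Case | s | a | b | In live births | In stillbirths | Share left out | Live births only | All births |
|---|---|---|---|---|---|---|---|---|
| Low | 2% | 2% | 5% | 21.8 | 1.1 | 1.1/22.9 = 5% | 2.00% | 2.06% |
| Middle | 2% | 1% | 10% | 10.9 | 2.2 | 2.2/13.1 = 17% | 1.00% | 1.18% |
| High | 4% | 1% | 15% | 10.7 | 6.7 | 6.7/17.3 = 38% | 1.00% | 1.56% |

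With 20% dropout (1110 × 0.8 = 888) every count falls by a fifth and the shares do not change. Wider assumptions (stillbirths 1 to 4%, anomalies in 5 to 20% of them) give 2 to 45%.

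The proportion itself moves only if anomalies are commoner in stillbirths than in live births. If b = a, the share left out is simply s (2 to 4%) and the live-birth proportion is unbiased. That anomalies are commoner in stillbirths is an assumption here; the protocol does not address it.

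**4. Direction of distortion.** Take two arms with the same 17.3 anomalies in 1110 births. In one, 6.7 affected infants are among 44.4 stillbirths, so the live-birth proportion is 10.7 / 1065.6 = 1.00%. In the other, those 6.7 are born alive, so stillbirths are 37.7 and the proportion is 17.3 / 1072.3 = 1.61%. Outcome 5 favours the arm in which the affected infants died, while the all-births proportion is 1.56% in both. This is a deliberate extreme to show direction, not an expected effect.

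**The case against.** The strongest reply is that these infants are not lost from the safety data. Outcome 6 counts abortions, intrauterine deaths and stillbirths, so an arm whose anomaly proportion looked better because affected fetuses died would show those deaths next to it. This stands as a partial safeguard. It does not restore the missing information: in the illustration above, stillbirths are 44.4 / 1110 = 4.0% against 37.7 / 1110 = 3.4%, and nothing in outcome 6 links that difference to anomalies.

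Three further objections also stand in part.

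- The protocol does not say that stillborn infants are examined for anomalies. That their anomalies are already recorded is a fair reading of the delivery procedures, not a stated fact. An all-births denominator may therefore include infants whose status is unknown.
- Using all births does not give a comparison exactly as randomised. Women enter at 16 to 24 weeks, and spontaneous abortion is itself an outcome after randomisation. The change reduces the selection without removing it.
- Every rate in the calculation is assumed, and no scenario here shows a changed conclusion between arms.

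A reader might infer two stronger points that the text does not support. One is that outcome 5 is the trial's principal measure of fetal safety. It is fifth of ten secondary outcomes, and the objective on fetal harm, "To demonstrate that the incidence of spontaneous abortions, intrauterine deaths/stillbirths, neonatal and maternal mortality and developmental delays", does not name anomalies. The sentence on national policy concerns AS+AQ safety data in general. The other is that the four stratification factors will leave mostly empty cells. That follows only if they are crossed. The wording equally allows four separate one-factor tables, and table layout may properly be left to the SAP.

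**Conclusion.** The point holds as a limited one. As written, outcome 5 leaves out anomalies in stillborn infants, conditions on an event after randomisation, and is narrower than the recording the protocol asks for. It undercounts anomalies and may distort the comparison of arms.

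The size cannot be derived from the protocol. Under the assumed rates in the table, about 5 to 38% of anomalies at birth are left out, or roughly 1 to 7 cases per arm of 1110 births. These figures rest wholly on the assumed rates, on one birth per woman, and on anomalies in stillborn infants being ascertained.

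The primary outcome and the sample size are untouched. This is an improvement worth making, not a threat to the trial's main conclusion.

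**What to change.** Redefine secondary outcome 5 along these lines: *the proportion of all births (live births plus stillbirths) with a clinician-confirmed congenital anomaly, by randomised arm, with a 95% confidence interval.* In addition:

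- state under Delivery and Postpartum Follow-up that the recording of deformities includes stillborn infants;
- report, by arm, the number of births with unknown anomaly status;
- keep the live-birth proportion as a supporting figure;
- say that spontaneous abortions after randomisation remain outside this outcome, and that it should be read alongside outcome 6.

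The cost is a reworded outcome, one clarifying sentence in the procedures and a changed denominator in one table. The sample size does not change. If sites would not otherwise have examined stillborn infants, there is also a small addition to delivery recording. The downside is that anomalies are less reliably ascertained in stillbirths, which is why the count of unknowns and the live-birth figure should stand beside the main one.

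### Secondary outcome 8 costs non-severe anaemia averted, whereas objective 5(2) costs all maternal anaemia averted; read literally, the narrower unit understates the effect

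*Protocol*

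**What the plan says.** Under Specific objectives in the Protocol, secondary objective 5 lists four units for the cost comparison: "1) severe maternal anaemia averted (2) maternal anaemia averted (3) peripheral malaria averted and (4) placenta malaria averted". Outcomes 7 to 10 under Study outcomes take these up in the same order. Outcome 7 is "Cost per severe maternal anaemia averted". Outcome 8, the counterpart of item (2), is "Cost per (non-severe) maternal anaemia averted". The bracketed word appears only there.

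The clinical outcomes give two haemoglobin cut-offs. The primary outcome is "Prevalence of severe maternal anaemia (Hb < 8g/dl) at 34 to 36 weeks of gestation". Secondary outcome 2 is "Prevalence of maternal anaemia (Hb < 11g/dl) at 34 to 36 weeks of gestation", which has no lower limit and so includes every severe case. The Protocol gives no haemoglobin limits for non-severe anaemia, and no clinical outcome measures a middle band.

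**The concern.** The objective and its outcome name different health units. Objective 5(2) asks for the cost per case of maternal anaemia averted; outcome 8 removes the severe cases from that count. Two analysts could follow the same Protocol and report different ratios.

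The literal unit is also a poor one. A middle band has two edges. A woman whose Hb would have been 7.5 and is instead 8.5 g/dl enters the band and scores as a case added. A woman who falls from 8.5 to 7.5 leaves it and scores as a case averted. Since Hb < 8 g/dl is the primary outcome, outcome 8 would subtract each success on the trial's own primary outcome from the effect.

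**Working it through.** **Inputs**
- Severe: Hb < 8 g/dl (primary outcome). Anaemia: Hb < 11 g/dl (outcome 2). The band Hb 8 to <11 is inferred from these two cut-offs; the Protocol does not state it.
- Severe anaemia in the SP-IPTp arm: 12% (Sample size).
- Prevalence of Hb < 11: not given. Assumed, and varied from 30% to 90%.
- Shift in mean Hb: assumed, 0.3 g/dl in either direction.

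**The plan's own figure.** No figure is attached to outcome 8. The sample size for the primary outcome reproduces: 2 × 0.12 × 0.88 × (1.960 + 1.282)² / 0.05² ≈ 888, against 887 stated (one-sided 0.025, 90% power). This point does not touch it.

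**Identity.** Band = P(Hb < 11) − P(Hb < 8), so

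band cases averted = Hb < 11 cases averted − severe cases averted.

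**Which movements count wrongly.** Take 1000 women, with 120 severe and (assumed) 400 in the band, and move 30:

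| Movement of 30 women | Severe averted | Band averted | Hb < 11 averted |
|---|---|---|---|
| Severe to band (benefit) | +30 | −30 | 0 |
| Band to severe (harm) | −30 | +30 | 0 |
| Band to ≥ 11 (benefit) | 0 | +30 | +30 |
| ≥ 11 to band (harm) | 0 | −30 | −30 |

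Only the first two rows, across Hb 8, have the wrong sign in the band column. The Hb < 11 column never has the wrong sign.

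**Net effect when the whole distribution shifts.** Let Hb be normal with 12% below 8 and a proportion p below 11. Then SD = 3 / (z(p) − z(0.12)) and mean = 8 − z(0.12) × SD. At p = 50%, z(0.12) = −1.175, so SD = 2.55 and mean = 11.0. A shift of +0.3 gives 21.9 severe and 46.8 Hb < 11 cases averted per 1000; the band shows 46.8 − 21.9 = 24.9.

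Cases averted per 1000 (a minus sign means added):

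| Assumed p | Band, +0.3 | Hb < 11, +0.3 | Band, −0.3 | Hb < 11, −0.3 |
|---|---|---|---|---|
| 30% | 9.7 | 22.2 | −9.5 | −23.0 |
| 50% | 24.9 | 46.8 | −21.6 | −46.8 |
| 60% | 29.8 | 56.0 | −23.0 | −54.0 |
| 80% | 25.4 | 61.1 | −6.4 | −51.6 |
| 85% | 18.8 | 57.5 | +4.4 | −45.7 |
| 90% | 7.8 | 50.1 | +19.7 | −36.6 |

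For a benefit and a given cost difference, the ratio per case is inflated by 46.8 / 24.9 = 1.9 at 50%, and by 1.9 to 2.4 over 30% to 80%. Under harm, the band shows less than half of the loss at every prevalence in the table, and the sign reverses at 85% and 90%. The low end rests on a wide spread (SD 4.6 g/dl at 30%).

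**The case against.** Outcomes 7 to 10 follow the four items of objective 5 in order, so the bracket may be only a loose label that sets item 8 apart from item 7. That is plausible, but the text does not say so, and on that reading the word can go without loss. It is also fair that the working details of a secondary cost outcome often belong in an analysis plan. Here, however, a stated outcome departs from its stated objective, which is more than an omitted detail.

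A reader might infer that the middle band generally rewards the worse strategy. An example can be built: hold Hb < 11 at an assumed 60% in both arms and let severe anaemia be 12% against 17%, the 5-point margin. The band is then 60 − 12 = 48% against 60 − 17 = 43%, and the worse arm appears to avert 5 per 100. But this lets nobody cross Hb 11, so all the change falls on the one boundary that counts wrongly. If instead the whole distribution shifts until severe anaemia reaches 17%, Hb < 11 rises to 68.2% and the band to 68.2 − 17 = 51.2%: the worse arm has 3.2 per 100 more band cases, the correct direction. The documents support neither the fixed 60% nor a general reversal.

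Nor does outcome 8 directly contradict outcome 2. One is a cost ratio and the other a prevalence; outcome 2 only supplies the definition. The conflict of text is with objective 5(2).

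**Conclusion.** The mismatch between outcome 8 and objective 5(2) stands on the text alone. The consequence depends on a literal reading with the Protocol's own cut-offs. On that reading the effect is understated whenever severe anaemia and all anaemia move in the same direction. In the normal-shift model a benefit shows at roughly half its size or less, while a change of sign needs harm together with an assumed Hb < 11 prevalence of about 85% to 90%. These sizes rest on the assumed prevalence, the assumed 0.3 g/dl shift and normality; only the 12% comes from the Protocol.

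The impact is minor. One secondary cost outcome is affected. The primary outcome, margin, sample size and outcome 2 are untouched, and because Hb is measured at 34 to 36 weeks in any case, either count can be derived later.

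**What to change.** Delete the bracketed word from outcome 8, so that it becomes the cost per case of maternal anaemia averted, with a case defined as Hb < 11 g/dl at 34 to 36 weeks, as in outcome 2 and objective 5(2). Keep Hb < 8 g/dl as the separate unit of outcome 7. Add a sentence that every severe case is also counted in outcome 8, so the two are not added together.

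If the band is truly intended, give its haemoglobin limits, justify it as a unit of benefit, and amend objective 5 to match.

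The cost is a one-word deletion and one added sentence. No new data are needed, and the sample size does not change.
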